### Eligibility criteria

College students from two universities in Colombia will be included in this study. Both undergraduate and graduate level students from any school at a university in Bogota, and students of psychology, medicine, nursing and education from a university in Bucaramanga will be eligible to participate and will be selected according to the criteria described in Table 1, which mirrors the criteria used in other studies of this type [41], especially initial investigations in new territories.

**Table 1 Tab1:** Eligibility criteria

Exclusion criteria:
Severe depressive symptoms > 19 on PHQ-9
Suicidal ideation or intent: Score of 2 or above on PHQ-9 question 9 Psychosis
Currently in psychological treatment for depression
On medication for less than 1 month
Alcohol or drugs misuse
Previous diagnosis of an organic mental health disorder
Depression preceding or coinciding a diagnosed medical condition
Inclusion criteria
18-year-old minimum
Mild to moderately severe depressive symptoms: (PHQ-9 score 10–19)

### User recruitment

An email will be sent to college students at two universities. Potential participants will be able to visit a website to receive information about the study, participation criteria, information about the treatment and how to get in contact to proceed with the study.

### Procedure

Once participants have read the study information, informed consent will be obtained from each user before screening and randomisation. Through the SilverCloud platform, participants will be instructed to type their name on the informed consent page, to indicate that they have read and understood the study information and agree to participate in the study. Thereafter, participants will complete measures for screening purposes, including the Patient Health Questionnaire (PHQ-9), Sociodemographic & Clinical History Questionnaire and Generalised Anxiety Disorder-7 (GAD-7). Thereafter, participants will be randomised based on their measures’ score through computer algorithms and they will be assigned to two groups – the active treatment group and waiting-list (WL) control group.

Those assigned to the active treatment will start the internet-delivered treatment immediately for seven weeks, while the WL participants’ treatment will start once the first group has finished the programme. Individuals not meeting the inclusion criteria at baseline assessment will be referred to other appropriate sources of face-to-face support at the student counselling service in the respective universities.

Any interactions or activities completed by the participants on the programme will be considered as a session, and it will be taken in the weekly feedback provided by the supporter. At the beginning of each session the participants will be asked to reflect on their previous session and complete the Helpful Aspects of Treatment Form (HAT). Furthermore, after week 7 the participants will complete Satisfaction with the Treatment (SAT).

Those who do not complete the research measures will receive automatic emails from the platform, to encourage them to use the programme. Likewise, supporters will send an email to the participants who do not complete the programme, and the research team will phone the participants who do not complete the measures.

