#### Study 2: Efficacy trial

The implementation of the culturally adapted programme and its evaluation among students using a randomised controlled trial methodology at two sites in Colombia.

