### Sample size

Power analysis, carried out in G-Power using significance level α = 0.05 and power = 0.80 determined 45 subjects would be required for each test condition (active group and waiting list) to observe a moderate effect (*d* = 0.50) post-treatment between groups [54].

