### Randomisation

After baseline screening, participants will be randomised and informed immediately about their group assignment. Randomisation will be handled by a computer algorithm administered by a person independent of the researchers. Figure 1 shows the CONSORT participant flow through the trial.

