#### Study 2: Efficacy trial

All analyses will be based on the intention-to-treat principle. Participants’ data will be included irrespective of treatment compliance. All of the data will be prepared and reviewed in SPSS.

Descriptive statistics will be used to analyse sociodemographic variables (e.g., gender and age). Chi-squared and t-tests will be used to examine demographic differences and clinical characteristics in the groups [67].

Effects will be tested at the 0.05 level. To assess significant changes over time, repeated measures ANOVAs will be performed for the primary outcome measure for depression (PHQ-9) and secondary outcome (GAD-7) [68]. The magnitude of effects within and between the two groups will be established by Cohen’s *d* statistic [67]. This will determine what is considered a small effect (*d* ≥ 0.2), a medium effect (*d* ≥ 0.5) and a large effect (*d* ≥ 0.8) [69].

Analyses will be carried out with participants who have clinically significant changes at the end of the intervention and at follow-up. The assessments will be made using pre-treatment scores, and these will be compared to post-treatment scores and follow-up scores on the outcome measures PHQ-9 and GAD-7. The analysis will be based on the Jacobson & Truax method, where a reliable change equals the difference pre-test and post-test, divided by the standard error of the difference [70].

Linear Mixed Model will be used for repeated measures (PHQ-9, GAD7) on each participant over time; it allows for a variety of correlation patterns (variance and covariance structures) to be explicitly modelled [71]. Also, it allows the measures on each subject to be used while accounting for missing data.

Participants’ responses in the HAT, identifying helpful and non-helpful events in the therapy and their impacts will be analysed qualitatively [66]. At the beginning, individual units of text will be analysed and identified out of their context. Next, these meaning units will be organised into helpful and non-helpful events and their impacts. Finally, these will be grouped into categories, which will be suitably named and defined.

Descriptive analysis will be used to analyse quantitative data from the SAT and their qualitative responses analysed using thematic analysis.

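### The role of baseline scores in allocation is unclear, and the planned models use baseline PHQ-9 as a repeated response without conditioning on it, which can cost power

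*Protocol article*

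**What the plan says.** **Allocation.** After the screening measures (PHQ-9, the sociodemographic and clinical history questionnaire, GAD-7), the Procedure section of the protocol article says that "participants will be randomised based on their measures’ score through computer algorithms". The Randomisation section says "Randomisation will be handled by a computer algorithm administered by a person independent of the researchers" and places this after baseline screening. It names no score, cut-point or site.

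**Sites.** Study 2 is run "using a randomised controlled trial methodology at two sites in Colombia". Under Eligibility criteria, the Bogota university admits undergraduates and graduates from any school, while "students of psychology, medicine, nursing and education from a university in Bucaramanga will be eligible to participate".

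**Analysis.** The planned analysis for Study 2 names repeated measures ANOVA for PHQ-9 and GAD-7, Cohen's d within and between groups, and a linear mixed model for the repeated scores, of which it says that "it allows for a variety of correlation patterns (variance and covariance structures) to be explicitly modelled". Table 3 lists baseline, post-treatment and follow-up as the PHQ-9 and GAD-7 occasions, so the baseline score is one of the repeated responses. Neither a baseline covariate nor a site term is named.

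**Size.** The Sample size section reports a calculation made "using significance level α = 0.05 and power = 0.80". Its result is 45 people per arm, and the stated purpose of that number is "to observe a moderate effect (*d* = 0.50) post-treatment between groups".

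**The concern.** There are two linked questions.

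First, what did the scores do in allocation? If they only admit people to randomisation, the Procedure sentence is loosely worded and nothing follows for the analysis. If they define strata or drive a minimisation, the analysis should condition on them; otherwise the variance that the design has balanced stays in the error term and the standard error is overstated. The article does not let a reader tell which applies.

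Second, whatever the answer, how is baseline PHQ-9 used? Including it as a repeated response differs from conditioning on it. If the treatment effect is read from an unconstrained group-by-time term, the test amounts to comparing mean changes, which subtracts the whole baseline score however weakly it predicts week 7. In a trial of 90 people the price can be considerable, and the score is already collected.

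**Working it through.** **Inputs from the protocol article (Sample size).** n = 45 per arm, d = 0.50 between groups post-treatment, alpha = 0.05, power = 0.80. Sidedness is not stated; two-sided is used unless noted.

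**Assumed inputs.** r, the correlation between baseline and week-7 PHQ-9; the documents give none, so 0.3, 0.5 and 0.7 are shown. The week-7 SD is set to 1 and the baseline SD is at first taken as equal to it. No dropout.

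**Step 1: the plan's own figure.** A two-sample t test with d = 0.50 needs 64 per arm two-sided or 51 one-sided for 80% power. At 45 per arm, power is 65% two-sided (76% one-sided). The stated 45 is not reproduced from the stated inputs. That is a separate problem; here it only supplies the n and d for the comparison below.

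**Step 2: three ways to use baseline.** Each reduces to a t test with noncentrality (0.50 / √v) × √(45/2), where v is the error variance on the week-7 scale:

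- week-7 scores alone: v = 1
- change contrast: v = 2(1 − r)
- baseline-adjusted (ANCOVA-type): v = 1 − r²

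| r | v, change | power, change | v, adjusted | power, adjusted | gain |
|---|---|---|---|---|---|
| 0.3 | 1.40 | 51% | 0.91 | 69% | 18 points |
| 0.5 | 1.00 | 65% | 0.75 | 77% | 12 points |
| 0.7 | 0.60 | 86% | 0.51 | 91% | 5 points |

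Worked line for r = 0.3: the change contrast has 0.50/√1.40 = 0.423 and noncentrality 0.423 × 4.743 = 2.00; the adjusted comparison has 0.50/√0.91 = 0.524 and noncentrality 2.49. Week-7 scores alone give 65% at every r.

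**Step 3: sensitivity to the equal-SD assumption.** The entry window of PHQ-9 10–19 may make the baseline SD smaller than the week-7 SD. With baseline SD equal to k times the week-7 SD, the change variance is 1 + k² − 2rk. For an assumed k = 0.75 it is 1 + 0.5625 − 0.45 = 1.1125 at r = 0.3 (power 60% against 69%) and 1 + 0.5625 − 0.75 = 0.8125 at r = 0.5 (74% against 77%). The gain shrinks. It cannot become a loss in error variance, because 1 + k² − 2rk − (1 − r²) = (k − r)², which is never negative.

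**Step 4: if scores were stratification factors.** A simulation under no effect used 90 participants, allocation stratified on two baseline bands and an assumed 0.3 SD site difference, at nominal 5%:

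| r | week-7 only | change | baseline-adjusted |
|---|---|---|---|
| 0.3 | 4.3% | 2.4% | 4.9% |
| 0.5 | 3.2% | 3.4% | 5.0% |
| 0.7 | 2.0% | 4.3% | 5.2% |

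The tests that do not condition on baseline are conservative; the adjusted one holds its level.

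**Step 5: site.** For two equal sites differing by an assumed δ of 0.1 to 0.5 SD, the site share of variance is (δ²/4)/(1 + δ²/4), that is 0.25% to 5.9%. Removing it moves the 65% to between 65% and 68%, a gain of 0 to 3 points.

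**The case against.** The strongest reply has four parts.

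**Baseline is already in the models.** This stands. A reader might infer that the analysis ignores baseline PHQ-9 altogether; it does not, since baseline is a repeated response in both. A mixed model that gives the arms a common baseline mean would have about the efficiency of ANCOVA, and the point would then cost almost nothing. But the article does not say that the means are constrained, and an ordinary repeated measures ANOVA does not constrain them.

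**The Procedure sentence may only mean that scores decide who is eligible.** This reading is open: the measures are introduced as screening measures, those who fail are referred elsewhere, and the Randomisation section mentions no score. Against it, GAD-7 is among those measures although Table 1 has no GAD-7 criterion, and the sentence attaches the scores to randomisation itself. A reader might go further and infer that allocation was not random. The documents do not support that; they describe a computer algorithm run by someone independent.

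**Covariate lists belong in an analysis plan that is not shown.** This is fair for the full list of terms. The point made here is narrower: the methods that the article does name leave a weaker contrast open, and the two descriptions of allocation do not match.

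**Site is not a stated allocation factor.** Correct. Different entry rules at the two sites do not bias a randomised comparison, and the power at stake is small. Site is worth including mainly against chance imbalance.

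**Conclusion.** The point holds in a limited form. The two accounts of allocation need reconciling. The week-7 comparison should condition on baseline, because an unconstrained change contrast gives up about 18, 12 or 5 points of power at r = 0.3, 0.5 or 0.7. Those sizes rest on an assumed r, equal SDs at the two times, two-sided testing, 45 per arm and no dropout. They are smaller if the baseline SD is the smaller one, and near nil if the mixed model sets the baseline means equal.

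A reader might infer from the allocation sentence that the trial's precision is definitely mis-stated, or that false positives are more likely. Neither follows. The standard errors are affected in this way only if scores were stratification factors, which no section clearly states, and the error is then conservative. Nor does adjustment by itself rescue the stated 80% power: at 45 per arm that would need r of about 0.55, before any dropout.

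**What to change.** 1. In Procedure and Randomisation, state the role that the scores actually played: eligibility only, or allocation factors as well. If the latter, name the scores, the cut-points and the method. The two sections should then say the same thing.
2. In the planned analysis, make the primary week-7 PHQ-9 comparison baseline-adjusted: either ANCOVA, or the mixed model with baseline as a covariate or with a common baseline mean. Include site and any actual allocation factor as fixed effects. Treat GAD-7 the same way with its own baseline.

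The randomisation method itself should not be rewritten. Recruitment began in August 2016 (Trial status), and a newly chosen stratified scheme would either describe something that the documents do not show was done or change allocation mid-trial.

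The cost is a few sentences. Baseline scores and site are already recorded, so no new data are needed. The model should be fixed before outcomes are compared by arm.

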### Randomisation

After baseline screening, participants will be randomised and informed immediately about their group assignment. Randomisation will be handled by a computer algorithm administered by a person independent of the researchers. Figure 1 shows the CONSORT participant flow through the trial.

**Fig. 1 Fig1:**
[figure not shown]
Participant flow CONSORT

#### Intervention space from depression

*Space from Depression* programme (*Yo puedo sentirme Bien* –Spanish version) consists of seven modules of cognitive-behavioural therapy (Table 2). The treatment includes self-monitoring, behavioural activation, cognitive restructuring, and challenging core beliefs. All modules have the same structure and format, which consist of quizzes, videos, educational content, activities with homework suggestions and a module review page. Also, users have a supporter, who will give feedback asynchronously [41].

**Table 2 Tab2:** Space from depression programme intervention description [41]

Module	Brief description
Getting started	This module outlines the basic premise of CBT, provides information about depression, and introduces some of the key ideas of Space from Depression. Users are encouraged to begin to chart their own current difficulties with depression.
Tune in I: getting to grips with mood	The focus in this module is on mood monitoring and emotional literacy. Users can explore different aspects of emotions, physical reactions, action and inaction, and how they are related.
Tune in II: spotting thoughts	This module focuses on noting and tracking thoughts. Users can explore the connection between their cognitions and their mood and record them graphically.
Change It I: boosting behaviour	This module focuses on behavioural change as a way to improve mood. Ideas about behavioural activation are included, and users can plan and record activities and chart their relationship with their mood.
Change It II: challenge your thoughts	This module supports users to challenge distorted or overly negative thinking patterns with thought records, as well as helpful coping thoughts.
Change It III: core beliefs	This module outlines the role that deeply held core beliefs could play in mood and depression. Users can use a range of interactive activities to identify, challenge and balance any unhelpful core beliefs.
Bringing It all together	In this final module, users are encouraged to bring together all the skills and ideas they have gathered so far, note their personal warning signs, and make a plan for staying well.

#### Wait list control group

Participants in the WL control group will receive treatment after seven weeks; therefore, this group will receive no treatment for the duration of the first seven weeks.

#### Supporters

Participants will be assigned a supporter, who will be a postgraduate student in clinical psychology with supervised experience in CBT with adults. Supporters will be trained in the *Space from Depression* (*Yo puedo sentirme bien*) platform and programme before starting their role as a supporter and will be supervised by an experienced clinical psychologist at the university. Each supporter will be assigned users and they will provide asynchronous post-session feedback of between 10 and 15 min per participant per session. The role of the supporter consists of motivating and providing feedback to the users. They can schedule the feedback at specific times once each week for a period of seven weeks.

#### Assessments

In study 1 cultural sensitivity will be determined through the ‘*top-down*’ revisions performed by the clinician researcher [name], together with translation and customisation. Ecological validity using experts and users will assess the cultural relevance of the *Space from Depression* (*Yo puedo sentirme bien*) programme using the Cultural Relevance Questionnaire (CRQ).

In study 2, the efficacy trial, participants will be assessed at baseline, post treatment, and at 3-month follow-up. Details of the measures are described in Table 3.

**Table 3 Tab3:** Study measures to be used

Study	Measure	Assessed variable	Time of assessment
Study 1 cultural validity	Cultural Relevance Questionnaire (CRQ)	Culturally adapted internet-delivered treatment	Completed by experts and users before the trial.
Study 2 efficacy trial	Patient Health Questionnaire (PHQ-9)	Depression symptoms	Baseline, post-treatment and follow- up
	Generalised Anxiety Disorder 7 (GAD-7).	Anxiety symptoms	Baseline, post-treatment and follow- up
	Sociodemographic & Clinical History Questionnaire	Gender, age, marital status, education, occupation, socioeconomic status and clinical history	Baseline
	Helpful and Hindering Aspects of Treatment (HAT)	Helpful and hindering aspects of treatment	After each session
	Satisfaction with Treatment (SAT)	Satisfaction with therapy	Post-treatment

Participants will be assessed at baseline through the Patient Health Questionnaire (PHQ-9), Sociodemographic & Clinical History Questionnaire and Generalised Anxiety Disorder-7 (GAD-7). At the beginning of each session participants will be asked to reflect on their previous session and complete the Helpful Aspects of Treatment Form (HAT). PHQ-9 and GAD-7 will be completed at week 7 and at follow-up (week 20 / 3 months). In addition, satisfaction with Treatment (SAT) will be administered at week 7.

### Measures

#### Study 1

***Cultural Relevance Questionnaire (CRQ):*** The Cultural Relevance Questionnaire is an instrument that evaluates a culturally adapted psychotherapy protocol. This questionnaire is based on cultural sensitivity and ecological validity theory by Bernal (2009) and Helms (2015) and their proposals for culturally adapted evidence-based practices. The CRQ has two sections, which includes a general assessment of the programme and an assessment of each module. Based on the Helms (2015) categories of functional equivalence, conceptual equivalence and linguistic equivalence, the first section evaluates eight areas [(a) language, (b) persons, (c) metaphors (d) content, (e) concepts, (f) goals, (g) methods and (g) context] [45] and is composed of five questions assessed on a 5-point Likert scale. The second section evaluates each modules content, examples, and personal stories, collecting qualitative observations based on the categories: functional equivalence, conceptual equivalence and linguistic equivalence.

#### Study 2

##### Screening measure

***Sociodemographic Information & Clinical History Questionnaire:*** This instrument was developed based on a previous version [55] and it collects details on the participants, such as data on the length of time that one is experiencing depression symptoms. Also, it collects data on participants’ experience of counselling/therapy and medication for depression. Data is collected on whether one has a previous diagnosis of an organic mental health disorder such as schizophrenia, psychosis and bipolar disorder. In addition, it contains items related to co-morbidity of depression with alcohol and drug misuse, and/or any recent medical diagnosis.

##### Primary outcome measure

***Patient Health Questionnaire (PHQ-9)*** [56]*:* PHQ-9 is a 9-item self-report measure that assesses the nine depression symptoms from the DSM-IV depression criteria. Each item is scored on a 4-point scale (0–3) and scores range from 0 to 27. The score can be used to describe the patient’s symptoms in one of five categories: none (0–4), mild (5–9), moderate (10–14), moderately severe (15–19), and severe (20–27). The PHQ-9 has been shown to have good reliability and validity in primary care populations, and to have good internal consistency and structural validity (α = 0.89, α = 0.86, respectively) [57]. PHQ-9 has been translated into Spanish and a Colombian version will be used in the current study (base on www.phqscreeeners.com/). The Spanish version of PHQ-9 has demonstrated reliability (α = 0.85) among Latinos in the U.S. [58, 59].

##### Secondary outcome measure

***General Anxiety Disorder (GAD-7)*** [60]*:* Comprises seven items measuring symptoms and severity of anxiety based on the DSM-IV diagnostic criteria. GAD-7 has shown reliability (α = 0.92) [61]. The GAD-7 has been culturally adapted into Spanish [62] and is available in a Spanish language Colombian version (www.phqscreeeners.com/).

##### Others measures

***Helpful Aspects of Therapy Form (HAT)*** [63, 64]*.* It is an instrument that assesses the most helpful and hindering events in the therapy. Participants are asked to describe any event or anything they engaged with in the session that was helpful or hindering for them.

***Satisfaction with Treatment (SAT)*** [65]*.* At post-treatment, participants will be asked to complete a satisfaction with treatment measure. SAT asks clients about positive and negative experiences with the internet-delivered treatment. SAT contains two questions asking participants to describe what participants most liked and least liked about the online treatment.

